### 2.3. Participant Recruitment and Study Procedures

This project will involve the consecutive enrollment of early TNBC patients with the onset or worsening of a PS (NRS ≥4) who meet the inclusion criteria of the study. 

The evaluation of QoL, perceived pain, and disability will be carried out at baseline (T0) and approximately 5 weeks after the start (T1) and at the end (T2) of PNE; finally, an additional assessment will be performed 6 months after the end of PNE. This evaluation will be conducted using validated questionnaires that measure the overall QoL of BC patients (European Organization for Research and Treatment of Cancer Quality of Life Questionnaire, Breast Cancer-Specific 23 [EORTCQLQ-BR23] questionnaire), pain (NRS), migraine and headaches (Headache Impact Test-6 [HIT-6] and MIgraine Disability ASsessment [MIDAS] questionnaires), and anxiety and depression (Hospital Anxiety and Depression Scale [HADS]).

At timepoints T0 and T2, a peripheral venous blood draw will be collected for the execution of a panel of blood chemical tests (CRP, ESR, Interleukin [IL]-6, IL-8, tumor necrosis factor [TNF]-α, and CGRP, as well as NLR calculation).

Our program involves the administration of a 10-session PNE program on a weekly basis (total of 10 weeks of intervention), in addition to the standard of care, according to the level of pain. The PNE sessions will be conducted by a physiotherapist expert in delivering PNE across different chronic pain populations, with more than 10 years of experience. Each session will be delivered in small groups (3–5 people) using a PowerPoint slide presentation and will last approximately one hour. A part of each session will be dedicated to questions and answers and personal discussion about personal experience.

The contents of the 10 sessions will be as follows:The concept of pain and its biological function.Common misconceptions about pain and its origin.The basics of the neurobiology of pain.What factors alter the perception of pain?The concept of the nervous system as a “protomet” and other metaphors.What happens when pain persists and becomes chronic?How can I train my nervous system?The importance of context, emotional aspects, and communication.The importance of stress management.Long-term pain management.

The program was structured starting from the books “*Explain pain*” [29] and “*Explain pain supercharged*” [30,31], written by the leading researchers on the topic of PNE.

To monitor adherence to the program, we will track in-person participation and monitor who downloads the slides of the PowerPoint presentation. Completing the questionnaires at the 3 timepoints will be a further adherence-monitoring tool.

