### 2.5. QoL Evaluation

The assessment of QoL, perceived pain, and disability in TNBC patients will be carried out at baseline and during and after training (T0, T1, and T2, respectively) using the following questionnaires (Table 1):EORTCQLQ-BR23: This questionnaire is derived from the integration of the general questionnaire for cancer patients (EORTC QLQ-C30) with topics specifically relevant to BC. It consists of 23 items grouped into 5 domains that evaluate the side effects of therapy, disorders at the level of the arm subjected to axillary lymph node surgery, disorders at the breast level, the perception of one’s body image, and sexual functioning. The scores are linearly converted into a scale from 0 to 100. For the functional scales (body image, sexuality, and future expectations), higher scores reflect a better condition, while for symptom scales, higher scores represent worse symptom levels [32,33].NRS: This one-dimensional intensity scale assesses the symptom of pain in a simple, immediate, and easily reproducible way (score from 0 to 10) [34].HIT-6: This test measures the impact of migraines on common daily activities. It was also validated in the Italian population. It consists of 6 questions concerning how often headaches have caused severe pain, how often they have interrupted daily activities, how often they have resulted in the complete interruption of activities with the need to rest, the presence of headache-related fatigue, irritability, and difficulty concentrating [35]. The possible values for each question are expressed through a Likert scale from 1 to 5 (never, rarely, sometimes, very often, and always) with which a numerical score value is associated (6, 8, 10, 11, 13), and therefore, the total score can range from 36 to 78.MIDAS: This questionnaire is widely used to measure the impact of headaches on the individual’s ability to be efficient at work, school, and social activities over the previous 3 months in terms of days of activity lost due to the headache [36]. It consists of 7 items, the first 5 of which evaluate the complete loss of or at least a 50% reduction in productivity (whether work, school, or household). The number of days lost is counted to give the final score. The frequency and intensity of headaches are explored in the last 2 questions. Based on the scores, a disability threshold from 1 to 4 is defined, where the fourth level, the most serious, starts from a score of 21.HADS: This scale is used to evaluate the presence and intensity of anxiety and depression symptoms in enrolled patients. This is the most widely used questionnaire for screening for anxiety and depression, validated both in the general population and in patients with a wide range of medical conditions, including patients with BC [37,38]. The scale consists of 14 items divided into two subscales (anxiety and depression) with 7 items each. Each item is assigned a score from 0 to 3, and the total score of each scale is 21 points, where a higher score refers to greater symptomatology. Specifically, a score from 11 to 21 indicates clinically significant cases of anxiety or depression.

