### 2.7. Statistical Analysis

#### 2.7.1. Sample Size

The population of the prospective group will consist of 30 consecutive early-stage TNBC patients recruited from our institution’s oncology department. Given the innovative nature of this study, which focuses exclusively on early-stage TNBC patients and utilizes PNE interventions administered by specialized staff, the sample size was determined based on prior prospective studies employing similar interventions [40].

To ensure the representativeness of our results and account for potential dropouts, we have incorporated a margin for sample attrition. Based on typical dropout rates observed in clinical studies, we anticipate a dropout rate of approximately 20%. Therefore, to achieve our target of 30 evaluable patients, we plan to initially recruit 36 patients (30/0.8), ensuring that the final sample size remains robust even if some participants withdraw from the study. This approach will help guarantee that our findings are statistically significant and reflective of the broader population of early-stage TNBC patients undergoing PNE interventions. 

Based on preliminary analyses regarding the study’s primary objective, we will evaluate whether the number of participants should be increased to 50 to identify any factors associated with a better or poor response to the study intervention.

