#### 2.7.2. Analysis

Detailed clinical and demographic variables will be recorded for each patient. Frequency tables and descriptive statistics (mean, standard deviation, percentage, median, range) will be used to summarize patient characteristics. 

Both the total score and the score for each domain will be calculated for each questionnaire, according to the nature of the questionnaire. The expected overall clinical improvement will be assessed based on the variation in the total scores of the administered assessment questionnaires at different timepoints (T0, T1, and T2). A positive response to PNE is defined as a 50% or greater improvement in patient-reported outcomes.

Changes in the levels of serum biomarkers between T0 and T2 (baseline and end of training) will be separately analyzed among patients who have responded to PNE (defined as an improvement in patient-reported outcomes of at least 50%) compared to non-responders using a generalized linear model in which the factors involved in the analysis will be the groups (responders/non-responders) and the timepoints (intra-group variable).

As variables of interest and covariates, demographic data, education level, comorbidities, risk factors for BC (e.g., body mass index, cigarette smoking), and menopausal status at diagnosis will be recorded. Additional covariates to be considered include anxiety and depression, which are closely linked to the perception of pain and the experience associated with it.

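### T2 and the 6-month assessment hang on the end of PNE with no stated date for women who stop attending, and completing the outcome questionnaires is listed as adherence, so the before-after change risks being seen mainly in finishers

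*Protocol article*

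**What the plan says.** Section 2.3 sets the first follow-up assessments at "approximately 5 weeks after the start (T1) and at the end (T2) of PNE". For the last one, "an additional assessment will be performed 6 months after the end of PNE". The intervention is described as "administration of a 10-session PNE program on a weekly basis (total of 10 weeks of intervention"). Section 2.5 ties the labelled timepoints to before, during and after training ("T0, T1, and T2, respectively"). Blood is drawn at T0 and T2 (Sections 2.3 and 2.6).

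For adherence, Section 2.3 states that "we will track in-person participation and monitor who downloads the slides of the PowerPoint presentation". It then adds: "Completing the questionnaires at the 3 timepoints will be a further adherence-monitoring tool".

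Section 2.7.2 bases the expected improvement on "variation in the total scores of the administered assessment questionnaires at different timepoints (T0, T1, and T2"). Section 2.7.1 expects about 20% dropout, targets 30 evaluable patients and recruits 36, with the stated aim of "ensuring that the final sample size remains robust even if some participants withdraw from the study".

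Section 2.2 says that patients who change their analgesics stay in follow-up and in the analysis. No section says the same, or the opposite, for patients who stop attending PNE.

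**The concern.** T1 has a time anchor. T2 and the 6-month assessment have an event anchor, and the event is finishing the program. T2 closes the primary comparison, carries the second blood sample and is the reference for the 6-month comparison in Section 2.4. If a woman stops attending and nobody is instructed to assess her at a set time, those data may never be collected, and no later analysis plan can recover them.

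The design makes this matter more. There is one group and the effect is a change from baseline, so selective loss feeds straight into the estimate. Women who leave a 10-week program during cancer treatment may well be those who feel worse or are not helped. Recruiting extra patients restores the count and does nothing about who is missing. Section 3 makes these results the trigger for a larger randomized trial.

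The adherence statement adds a second confusion. Returning an outcome form shows that data exist. It does not show that the program was received. Section 3 says that the study will inform feasibility, and for that purpose the two need to be kept apart.

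**Working it through.** **1. The anchors side by side**

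| Assessment | Anchor in the protocol article | Stated rule for a woman who stops attending |
|---|---|---|
| T1 | about 5 weeks after the start of PNE | none needed: the date exists for every starter |
| T2 (questionnaires and blood) | end of PNE | none |
| Last assessment | 6 months after the end of PNE | none |

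Ten weekly sessions imply a nominal T2 near week 10. What is absent is a statement that T2 is taken then whether or not the woman still attends, or how it moves if her program runs late.

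**2. The plan's own recruitment figure**

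Inputs (Section 2.7.1): 30 evaluable patients, 20% dropout, 36 recruited.

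- 30 × 1.2 = 36, the stated number.
- 30 / 0.8 = 37.5, so 38. The printed expression does not give 36. That is a separate point, and the steps below use the planned 36.

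**3. How many could lack T2**

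36 × 0.8 = 28.8, about 29 with T2. 36 − 29 = 7 without it, if every expected dropout misses T2.

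**4. What this does to a response rate**

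The document gives no expected response rate, so the rates here are assumptions. The lower bound counts all missing women as non-responders (responders / 36). The upper bound counts them all as responders ((responders + missing) / 36).

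| Dropout | With T2 | Assumed responders | Rate in those with T2 | Lower bound, all 36 | Upper bound, all 36 |
|---|---|---|---|---|---|
| 10% | 32 | 16 | 50% | 16/36 = 44% | 20/36 = 56% |
| 20% | 29 | 14 | 48% | 14/36 = 39% | 21/36 = 58% |
| 30% | 25 | 12 | 48% | 12/36 = 33% | 23/36 = 64% |

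At 20% dropout with other assumed rates, 9/29 (31%) is compatible with 25% to 44%, and 20/29 (69%) with 56% to 75%. With 38 recruited instead of 36, 15/30 (50%) is compatible with 15/38 = 39% to 23/38 = 61%, so the picture does not depend on the recruitment figure.

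**5. What this does to a mean change in NRS**

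Assume a 2.0-point improvement in women with T2. The mean over all starters is (1 − d) × 2.0 + d × m, where d is the dropout rate and m the improvement in dropouts.

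| Dropout | m = 0 | m = −1 (worse by 1 point) |
|---|---|---|
| 10% | 1.8 | 1.7 |
| 20% | 1.6 | 1.4 |
| 30% | 1.4 | 1.1 |

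At 20% and m = 0, 2.0 / 1.6 = 1.25, so the figure in finishers is 25% higher than in all starters. If dropouts improve as much as the others (m = 2.0), there is no bias.

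**6. The adherence measures**

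Three are listed: attendance, slide downloads and questionnaire completion. The first measures receipt of the program and the second gives indirect support. The third measures whether the outcome was observed. A woman can attend all 10 sessions and miss T1, or stop attending and still return every form. In both cases the third measure points away from the first.

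**The case against.** The strongest reply is that several damaging conclusions are not in the text.

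- A reader might infer an analysis restricted to completers. No analysis set is named and evaluable is not defined. Both may sit in the full protocol or an analysis plan that is not shown, so their absence is no finding. This stands.
- A reader might infer that T2 has no date at all for a woman who stops, or that it could fall before T1. The 10-week program supplies a natural date near week 10, and nothing supports the earlier one. This stands. What is missing is an explicit rule.
- A reader might infer that adherence is defined by questionnaire completion. Attendance and downloads come first, completion is only an additional tool, and no adherence score or threshold exists. This stands, so feasibility can still be judged from attendance.
- The three timepoints in the adherence sentence match the three labelled ones, and the 6-month visit is stated separately. That is not an error.
- The 20% refers to withdrawal from the study. Some of those women may refuse any contact, so the share of missing T2 data that a better rule would recover is unknown. This stands and limits the size.

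The reply does not dispose of the point by calling it wording for a fuller document. The event anchor and the adherence statement are things the article affirmatively says. When an outcome is collected is a matter of design, and an analysis plan cannot repair an assessment that was never made.

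**Conclusion.** The point holds in a limited form. T2 and the 6-month assessment depend on the end of PNE without a stated date for women who stop, and the only stated response to about 20% dropout is over-recruitment. The primary change therefore risks being observed mainly in women who finish. The documents do not show that it will be analysed in them alone.

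At the plan's own 20%, about 7 of 36 women could lack T2, taking every dropout as a missing T2. On an assumed 48% response in the other 29, the rate among all 36 could lie anywhere from 39% to 58%. The bounds run both ways. An overstatement, such as the 25% on mean NRS, needs the further assumption that dropouts did worse.

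Listing questionnaire completion as adherence is a lesser fault. It blurs one of three measures and should be separated. The change is worth making, because it is cheap and the data cannot be recovered afterwards.

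**What to change.** - Date T2 at the article's own 10 weeks from the first session, with a stated window, and the last assessment 6 months after that date.
- Apply both to every woman who attended at least one session, whether or not she still attends, unless she withdraws consent.
- Base the primary change on all starters.
- Measure adherence by sessions attended out of 10, with slide downloads as support.
- Report questionnaire completion separately as data completeness, over T0, T1, T2 and the 6-month assessment.

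Costs: a few sentences in the protocol and follow-up contact with women who have stopped. T2 blood can be obtained only from those who agree to attend. For anyone whose program runs late, T2 would precede her last session, which slightly changes the meaning of the comparison between T2 and six months in Section 2.4. The reported effect may be slightly smaller.

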### 2.4. Objectives

Primary objective:The primary objective of the project is to evaluate, through the use of validated questionnaires, whether the implementation of a dedicated PNE and cognitive training program can lead to clinical improvement in terms of QoL and pain in patients with early-stage TNBC.

Secondary objectives:To assess the impact of PNE on headaches/migraine in patients affected by this condition prior to the start of the program.To evaluate the impact of PNE on anxiety/depression symptoms according to the score of the planned scales.To investigate whether serum levels of inflammatory biomarkers correlate with PSs.To investigate whether serum levels of inflammatory biomarkers before and after PNE treatment correlate with the response to PNE.To compare the results at the end of PNE (T2) with those at six months after the end of the program.

### 2.5. QoL Evaluation

The assessment of QoL, perceived pain, and disability in TNBC patients will be carried out at baseline and during and after training (T0, T1, and T2, respectively) using the following questionnaires (Table 1):EORTCQLQ-BR23: This questionnaire is derived from the integration of the general questionnaire for cancer patients (EORTC QLQ-C30) with topics specifically relevant to BC. It consists of 23 items grouped into 5 domains that evaluate the side effects of therapy, disorders at the level of the arm subjected to axillary lymph node surgery, disorders at the breast level, the perception of one’s body image, and sexual functioning. The scores are linearly converted into a scale from 0 to 100. For the functional scales (body image, sexuality, and future expectations), higher scores reflect a better condition, while for symptom scales, higher scores represent worse symptom levels [32,33].NRS: This one-dimensional intensity scale assesses the symptom of pain in a simple, immediate, and easily reproducible way (score from 0 to 10) [34].HIT-6: This test measures the impact of migraines on common daily activities. It was also validated in the Italian population. It consists of 6 questions concerning how often headaches have caused severe pain, how often they have interrupted daily activities, how often they have resulted in the complete interruption of activities with the need to rest, the presence of headache-related fatigue, irritability, and difficulty concentrating [35]. The possible values for each question are expressed through a Likert scale from 1 to 5 (never, rarely, sometimes, very often, and always) with which a numerical score value is associated (6, 8, 10, 11, 13), and therefore, the total score can range from 36 to 78.MIDAS: This questionnaire is widely used to measure the impact of headaches on the individual’s ability to be efficient at work, school, and social activities over the previous 3 months in terms of days of activity lost due to the headache [36]. It consists of 7 items, the first 5 of which evaluate the complete loss of or at least a 50% reduction in productivity (whether work, school, or household). The number of days lost is counted to give the final score. The frequency and intensity of headaches are explored in the last 2 questions. Based on the scores, a disability threshold from 1 to 4 is defined, where the fourth level, the most serious, starts from a score of 21.HADS: This scale is used to evaluate the presence and intensity of anxiety and depression symptoms in enrolled patients. This is the most widely used questionnaire for screening for anxiety and depression, validated both in the general population and in patients with a wide range of medical conditions, including patients with BC [37,38]. The scale consists of 14 items divided into two subscales (anxiety and depression) with 7 items each. Each item is assigned a score from 0 to 3, and the total score of each scale is 21 points, where a higher score refers to greater symptomatology. Specifically, a score from 11 to 21 indicates clinically significant cases of anxiety or depression.

**Table 1 jpm-14-00711-t001:** Questionnaires that will be used for the assessment of QoL, perceived pain, and disability in TNBC patients at baseline and during and after training.

Domain	Questionnaire	Description	Scaling	Ref.
QoL	EORTCQLQ-BR23	23 items on side effects, disorders at the axilla and the breast(s), body image, and sexual functioning	From 0 to 100	[32,33]
Pain	NRS	one-dimensional intensity scale	From 0 to 10	[34]
Psychological	HADS	14 items on anxiety and depression	From 0 to 21 (for each 7-point scale)	[37,38]
Headache	HIT-6	6 questions on the impact of migraine on common daily activities	From 36 to 78	[35]
Headache	MIDAS	7 items on the impact of headaches on individual efficiency at work, school, and social activities	From to 28	[36]

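### MIDAS looks back 3 months but is repeated about 5 and 10 weeks after PNE starts, so its T1 and T2 scores still count pre-PNE headache days and understate any improvement

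*Protocol article*

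**What the plan says.** The first secondary objective in section 2.4 is "To assess the impact of PNE on headaches/migraine in patients affected by this condition prior to the start of the program". Two headache instruments are listed, HIT-6 and MIDAS.

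Section 2.5 describes MIDAS as covering work, school and "social activities over the previous 3 months in terms of days of activity lost due to the headache", and on scoring it says: "The number of days lost is counted to give the final score". No shorter recall period is given for this study.

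The same section says that assessment "will be carried out at baseline and during and after training (T0, T1, and T2, respectively) using the following questionnaires", and MIDAS is on that list. Section 2.3 places the two later visits "approximately 5 weeks after the start (T1) and at the end (T2) of PNE". The program has 10 weekly sessions over 10 weeks. Section 2.3 also schedules one more assessment 6 months after PNE ends.

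Section 2.7.2 bases clinical improvement on the "variation in the total scores of the administered assessment questionnaires at different timepoints (T0, T1, and T2"), and adds: "A positive response to PNE is defined as a 50% or greater improvement in patient-reported outcomes". It names neither an instrument nor a timepoint for that 50% rule. The last secondary objective in section 2.4 compares T2 with the 6-month assessment.

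**The concern.** A questionnaire that counts events over a fixed look-back period measures the effect of an intervention cleanly only if the whole period lies after the intervention began. Here the look-back is about 13 weeks and the repeat readings come at about 5 and 10 weeks. Headache days already counted in the T0 score are counted again at T1 and T2, so part of the baseline reappears as outcome.

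Two things are at stake. First, MIDAS change from T0 is pulled toward no effect, in what may be a small subgroup of a study planned around 30 patients. Second, the pre-PNE share shrinks from T1 to T2 and is zero at 6 months. A benefit that is immediate and then stable would therefore look like one that keeps growing, which distorts the planned comparison of T2 with 6 months.

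**Working it through.** The plan gives no figure of its own to reproduce on this point. The check is an overlap calculation.

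**Inputs**
- Look-back L: 3 months (section 2.5), taken as 13 weeks = 91 days; 90 and 92 days also tried.
- Time since PNE start, t: 35 days at T1 (section 2.3, about 5 weeks; 28 to 42 days tried) and 70 days at T2 (10-week program; 63 days if counted from the first to the tenth weekly session).
- Assumptions, not in the documents: a constant rate of lost days over the 3 months before T0, T0 at about the start of PNE, and an effect that is immediate and then stable. A delayed effect would make the dilution worse.

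**Formulas**
- Pre-PNE share of the window = (L − t)/L.
- Observed fall = true fall × t/L.
- True fall needed to score 50% = 0.5/(t/L).

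**Results for L = 91 days**

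| | T1 (t = 35) | T2 (t = 70) | 6 months after PNE |
|---|---|---|---|
| Pre-PNE share | 56/91 = 61.5% | 21/91 = 23.1% | 0% |
| Observed fall, complete relief | 35/91 = 38.5% | 70/91 = 76.9% | 100% |
| Observed fall, true 50% fall | 0.5 × 35/91 = 19.2% | 0.5 × 70/91 = 38.5% | 50% |
| True fall needed to score 50% | 0.5/0.385 = 130%, not attainable | 0.5/0.769 = 65% | 50% |

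**Sensitivity to timing**
- With T1 anywhere from week 4 to week 6 and L from 90 to 92 days, the ceiling at T1 is 30% to 47%.
- With T2 at day 63, the ceiling at T2 is about 69%.

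**Sensitivity to the pre-entry headache rate**
- Rate doubled in the last 4 weeks before T0: baseline = 28 × 2 + 63 = 119 units. Carried into T1: 28 × 2 + 28 = 84, ceiling 1 − 84/119 = 29.4%. Carried into T2: 21 × 2 = 42, ceiling 1 − 42/119 = 64.7%.
- All lost days in the last 4 weeks: ceiling 0% at T1 and 1 − 21/28 = 25% at T2.
- Falling rate: the T1 ceiling reaches 50% if the rate in the earliest 5 weeks of the baseline window is at least 56/35 = 1.6 times that in the last 8 weeks. It also does so if the last-4-week rate is a quarter of the earlier rate: baseline 7 + 63 = 70, carried over 7 + 28 = 35.

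**T2 against 6 months**
For a stable true 50% fall, T2 MIDAS is 21/91 + 0.5 × 70/91 = 0.615 of baseline. The 6-month window covers roughly months 3 to 6 after PNE and reads 0.50. The apparent further fall is 1 − 0.50/0.615, about 19%, with no real change.

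**HIT-6 as the alternative at T2**
Section 2.5 gives a range of 36 to 78. A raw score can halve only if the baseline is at least 2 × 36 = 72. The 50% rule is therefore out of reach on HIT-6 for any baseline below 72.

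**Table 1**
The table prints an upper limit of 28 for MIDAS. The text defines a count of lost days over 3 months, drawn from five items, with the worst grade starting at 21. Nothing in that definition stops the count at 28.

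**The case against.** The strongest reply is that the protocol never says a patient will be classed as a responder on MIDAS at T1. The 50% rule names no instrument or visit, and the one analysis described that uses responder status, the biomarker model, works on T0 and T2. At T2 the rule can be met on MIDAS at a constant headache rate. This stands. A reader might infer that real responders will be recorded as non-responders, but the documents do not fix that. The dilution of MIDAS change does not depend on the 50% rule.

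A reader might also infer that even complete relief can never reach 50% at T1. That needs a stable or rising headache rate before T0. Entry within 4 weeks of pain starting or getting worse makes a falling rate less likely, but the pain that worsened need not be headache, so the condition has to be stated.

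It would also go too far to say that the whole headache objective is diluted. HIT-6 is given at every visit and is not shown to be affected. The documents state no recall period for it, so they do not show it to be free of overlap either.

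The bias in comparisons with T0 is toward no effect, so it cannot by itself produce a false claim of benefit there. That is right for T0 comparisons but not for T2 against 6 months, where it creates apparent improvement.

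Finally, a reader might infer from Table 1 that the eCRF will cut off severe scores at 28. Section 2.8 describes no range limits, and the table cell is itself incomplete, so this is only a table correction.

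**Conclusion.** The concern holds. The overlap of the MIDAS window with pre-PNE time follows directly from the stated recall period and visit schedule: about 62% of the window at T1 and 23% at T2. Assuming a constant headache rate before T0 and an immediate effect, a true 50% fall in lost days reads as about 19% at T1 and 38% at T2. Complete relief reads as about 38% at T1, and a true 65% fall is needed to score 50% at T2. The same stable benefit moves from about 0.62 of baseline at T2 to 0.50 at 6 months without any further change.

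The reach is limited. MIDAS is one of two headache instruments serving a secondary objective, and the NRS and BR23 measures of the primary objective are not affected. The point should be settled before the data are analysed, but it does not threaten the main question of the study.

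**What to change.** - Exclude T1 MIDAS from the improvement analysis and from any 50% response classification.
- Label T2 MIDAS as descriptive and state that its window is partly pre-PNE.
- Make 6-month MIDAS against T0 the MIDAS comparison, interpreted as a sustained effect, and add that timepoint to section 2.7.2, which lists only T0, T1 and T2.
- Do not read MIDAS change from T2 to 6 months as improvement.
- Analyse HIT-6 at T2 as score change, not with the 50% rule, and state its recall period.
- Reconcile the MIDAS range in Table 1 with the days-lost count in section 2.5.

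The cost is wording only, because section 2.3 already schedules the 6-month assessment. The price is scientific: the MIDAS result comes later, is exposed to dropout, and measures persistence of benefit, not the effect at the end of the program.
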